# Comparison Between Conventional Intervention and Non-immersive Virtual Reality in the Rehabilitation of Individuals in an Inpatient Unit for the Treatment of COVID-19: A Study Protocol for a Randomized Controlled Crossover Trial

**DOI:** 10.3389/fpsyg.2021.622618

**Published:** 2021-02-24

**Keywords:** coronavirus, telerehabilitation, virtual reality exposure therapy, hospitals, rehabilitation, autonomic nervous system, physical functional performance

## Abstract

**Background:** The new human coronavirus that leads to COVID-19 (coronavirus disease 2019) has spread rapidly around the world and has a high degree of lethality. In more severe cases, patients remain hospitalized for several days under treatment of the health team. Thus, it is important to develop and use technologies with the aim to strengthen conventional therapy by encouraging movement, physical activity, and improving cardiorespiratory fitness for patients. In this sense, therapies for exposure to virtual reality (VR) are promising and have been shown to be an adequate and equivalent alternative to conventional exercise programs.

**Aim:** This is a study protocol with the aim of comparing the conventional physical therapy intervention with the use of a non-immersive VR software during COVID-19 hospitalization.

**Methods:** Fifty patients hospitalized with confirmed diagnosis of COVID-19 will be divided in two groups under physiotherapy treatment using conventional or VR intervention: Group A: participants with COVID-19 will start the first day of the protocol with VR tasks in the morning and then in the second period, in the afternoon, will perform the conventional exercises (*n* = 25) and Group B: participants with COVID-19 will start the first day with conventional exercises in the morning and in the second period, in the afternoon, will perform activity with VR (*n* = 25). All participants will be evaluated with different motor and physiologic scales before and after the treatment to measure improvements.

**Conclusion:** Considering the importance of benefits from physical activity during hospitalization, VR software shows promise as a potential mechanism for improving physical activity. The results of this study may provide new insights into hospital rehabilitation.

**Trial Registration:**
ClinicalTrials.gov, identifier: NCT04537858. Registered on 01 September 2020.

## Introduction

At the end of 2019, the world saw the emergence of a new human coronavirus that was spreading rapidly and with a high degree of lethality (Huang et al., 2020; Singhal, 2020). The virus was called SARS-CoV-2 (severe acute respiratory syndrome coronavirus 2), responsible for causing COVID-19 (coronavirus disease 2019) (Baig et al., 2020; Chen et al., 2020; Weston and Frieman, 2020; Zhou et al., 2020).

The majority of people who acquired the virus did not show any significant symptoms (Chen et al., 2020), whereas 15% of people who had the virus developed mild or moderate symptoms, the most common of which were fever (85–90%), cough (65–70%), fatigue (35–40%), dyspnea (15–20%), and myalgia (10–15%) (Guan et al., 2020; Huang et al., 2020; Madabhavi et al., 2020).

Different from existing viruses that cause SARS and Middle East respiratory syndrome (De Wit et al., 2016; Madjid et al., 2020; Paules et al., 2020), COVID-19 symptoms cause early complications such as acute respiratory distress syndrome sepsis and multiple organ failure requiring admission to the intensive care unit (Yang et al., 2020), which might lead to overload of care services in public and private sectors (Sheehy, 2020; Wu and McGoogan, 2020). In addition to the high rate of hospitalization, a major difference from COVID-19 is the average hospitalization period, which is usually 12 days (Guan et al., 2020) in an outpatient setting, and if there is a need for intensive care, this period can be extended to ~22 days (Yang et al., 2020; Zhou et al., 2020).

Considering the need for hospitalization, the rehabilitation protocol includes multidisciplinary teams, with physiotherapy treatment being recognized as an important intervention. According to Lew et al. (2020), physiotherapy in the treatment of COVID-19 consists mainly of physical care where the patient may have low physical fitness, shortness of breath after exertion, and muscle atrophy (including respiratory muscles, trunk, and limb muscles). It is important to emphasize that hospitalized patients receive physiotherapy treatment at the bedside once a day for those in moderate need, and three times a day for those in high need (Smith et al., 2020). This intervention uses progressive exercises that can be selected so that patients can gradually recover the level of activity observed before the onset of the disease (Zhao et al., 2020).

Thus, innovations using virtual reality (VR) during intervention in outpatient rehabilitation services are important to minimize functional deficits that might otherwise lead to permanent disability (Boldrini et al., 2020; Coraci et al., 2020). Where other VR systems are cost-prohibitive, low-cost VR promotes an important cost-effectiveness to public health service, providing an effective tool to health workers to work as adjunctive to routine with inpatients with less effort in patient handling (Zanaboni et al., 2016; Ford et al., 2018; Shields et al., 2018). Therefore, the use of computational tasks in a virtual environment can be an interesting option (de Freitas et al., 2019; de Moraes et al., 2020; Leal et al., 2020; Stam et al., 2020).

The use of tasks in virtual environments has grown a lot in recent years, showing itself as an adequate alternative and equivalent to conventional exercise programs (Bond et al., 2019; García-Bravo et al., 2019), and the benefits of physical exercise associated with VR have shown a promising impact in improving the patient's self-efficacy for physical training, in addition to providing an engaging environment for the patient (Dias et al., 2019). Moreover, the VR can enable the rehabilitation team to control different variables such as speed, task size, and more important creative tasks to promote motivation (Fernani et al., 2017; Prado et al., 2017; da Silva et al., 2020b).

In addition to improve motor performance and functionality, it has been shown to increase motivation and consequent engagement to rehabilitation. In a recent systematic review of VR and video games for cardiac rehabilitation programs, all publications pointed to improvement of the motivation and engagement to therapy as the main advantage derived from the use of VR rehabilitation; the subjects reported that it was a fun and interactive form of treatment (García-Bravo et al., 2019).

Despite positive existing studies with the use of VR in different respiratory disabilities, such as chronic obstructive pulmonary disease (Mazzoleni et al., 2014; Jung et al., 2020; Rutkowski et al., 2020), exercises training on thoracic hyperkyphosis, and respiratory parameters in young women (Taslimipour et al., 2020), research in a hospital environment is still scarce, and more studies are needed to verify benefits and possible applications.

According to Bond et al. (2019), the requirement of physical exercise inherent to a video game's activities (exergames) is shown to have a promising impact in improving patient self-efficacy for exercise training using digital hardware (e.g., the Nintendo Wii® or the Xbox Kinect®), once interactive VR promotes increased heart rate (HR), rating of perceived exertion (RPE), and physical activity (Bond et al., 2019; García-Bravo et al., 2019). Therefore, patients using exergames rather than conventional exercise routines (e.g., walking, running, or cycling) have been reported to exercise for longer periods, meeting moderate to vigorous physical activity levels, with the perception of “work” being lower or less intense, and more enjoyable, contributing to healthier lifestyle initiatives (Glen et al., 2017; Gomez et al., 2018; Polechoński et al., 2019).

Considering the above deliberations, we have organized a randomized controlled crossover protocol to investigate rehabilitation of patients hospitalized with COVID-19. The aim of this protocol is to find out whether the motor performance, functionality, engagement, motivation, and physiological parameters are different during conventional or virtual intervention. We are interested in comparing conventional cardiovascular and musculoskeletal physical therapy interventions with typical movements and mobilization in different postures such as sitting and standing, using VR software that provides a game in which the participants continually move upper limbs and trunk to finish a motor task proposed by the application. Participants will therefore alternate their rehabilitation intervention (conventional or virtual) during their hospitalization period. Furthermore, we will be using a satisfaction scale to verify the level of engagement in the therapy during the rehabilitation program.

We hypothesize that all participants will show improvement in motor performance, functionality, and physiological parameters independent of the intervention (conventional or virtual environment); however, the use of a virtual task will provide more engagement and motivation. If our hypothesis is proven, it might be the beginning of a technological innovation in cardiorespiratory rehabilitation in hospitals.

## Methods/Design

We registered this trial on ClinicalTrials.gov (NCT04537858). This article has been reported in accordance with the Standard Protocol Items Recommendations for Interventional Trials (SPIRIT) (Chan et al., 2013a,b; Tables 1, 2).

**Table 1 T1:** SPIRIT: description of the study protocol, schedule of enrolment, interventions, and assessments.

**Study period**												
	**Enrolment**	**Allocation**	**Post-allocation**								**Close-out**	
**Timepoint**	**0**	**0**	**t**_**1**_	**t**_**2**_	**t**_**3**_	**t4**	**t5**	**t6**	**t7**	**t8**	**t9**	**t10**
			**1 day**	**2 days**	**3 days**	**4 days**	**5 days**	**6 days**	**7 days**	**8 days**	**7 days after discharge**	**1 month after discharge**
**ENROLLMENT**												
Eligibility screen	X											
Informed consent	X											
Assessment scales	X											
Allocation		X										
**INTERVENTIONS**												
Group A												
Group B												
**ASSESSMENT SCALES**												
Barthel Index	X									X	X	X
Timed Up and Go (TUG)			X							X	X	X
Medical Research Council (MRC)			X							X	X	X
Brunel Mood Scale (BRUMS)			X							X	X	X
Enjoyment Scale (ES)			X	X	X	X	X	X	X	X	X	X
Visual Analogical Satisfaction Scale (VASS)			X	X	X	X	X	X	X	X	X	X
**PHYSIOLOGICAL ASSESSMENT**												
Heart rate variability (HRV)			X							X	X	X
The Borg Rating of Perceived Exertion (Borg scale)			X	X	X	X	X	X	X	X	X	X
Oxygen saturation (Sao_2_)			X	X	X	X	X	X	X	X	X	X
Respiratory rate (RR)			X	X	X	X	X	X	X	X	X	X
Heart rate (HR)			X	X	X	X	X	X	X	X	X	X

**Table 2 T2:** Trial characteristics based on WHO Trial Registration Data Set.

**Data category**	**Trial information**
Primary registry and trial identifying number	ClinicalTrials.gov, ID: NCT04537858
Date of registration in primary registry	01 September 2020 on
Secondary identifying numbers	Ethics Committee of the Federal University of São Paulo, under the number CAAE: 33244620.5.0000.5505
Source(s) of monetary or material support	Coordenação de Aperfeiçoamento de Pessoal de Nível Superior–Brasil
Primary sponsor	University of São Paulo
Secondary sponsor(s)	NA
Contact for public queries	[name], [name]
Contact for scientific queries	[name], [name]
Public title	Conventional intervention and non-immersive virtual reality in COVID-19
Scientific title	Comparison Between Benefits of Conventional Intervention and Non-immersive Virtual Reality in the Rehabilitation of Individuals in an Inpatient Unit for the Treatment of COVID-19: A Study Protocol
Country of recruitment	Brazil
Health condition(s) or problem(s) studied	COVID-19
Interventions	Group A: Subjects will start the first day of the protocol with virtual reality intervention and then in the second period will perform the conventional intervention. Group B: Subjects will start the first day with conventional intervention and in the second period will perform activity with virtual reality intervention. Both therapies will be performed on the same day at different times for 10 consecutive days
Key inclusion and exclusion criteria	Inclusion criteria: Agreement to participate in the research from themselves by signing consent form, a clinical and posterior blood analysis of COVID 19 infection, adults with age ranging from x to xx years. Exclusion criteria: Do not understand the tasks; the understanding of the task will be evaluated through five attempts at each task in virtual reality; do not want to use virtual reality task; was not in a physical condition to practice a functional task; use of an intravenous device that makes it impossible to move the arms; cardiac arrhythmias and atrioventricular block; congenital anomalies, such as congenital heart defects, pulmonary malformations; and patients who use drugs that interfere with ANS, such as antiarrhythmic agents
Study type Interventional allocation	Randomized
Masking	Randomization and data analyst
Assignment	Crossover
Primary purpose	Treatment
Date of first enrolment	June 2020
Target sample size	50
Recruitment status	Recruiting
Primary outcome(s)	Functional capacity improvement
Key secondary outcome(s)	HRV improvement

### Overview of the Study Design

A randomized controlled crossover protocol will be conducted, and all participants will undertake interventions in non-immersive VR–virtual intervention (with a serious game in web platform) and conventional intervention (with cardiovascular and musculoskeletal conventional physical therapy). All participants will be randomly divided in two groups: Group A will start the first day of the protocol with virtual intervention in the morning (their first rehabilitation session of the day) and the conventional intervention in the afternoon (their second rehabilitation session of the day). Group B will perform the reverse protocol (i.e., starting the first day of the protocol with conventional intervention in the morning and the virtual intervention in the afternoon) in a crossover design, during the hospitalization period (varying from 2 to 8 days according to individual needs). We chose two interventions per day, as it is the protocol of the Hospital of the Federal University of São Paulo (Hospital São Paulo) for inpatients in ambulatory unit.

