### Recruitment

Fifty participants will be recruited through the Hospital of the Federal University of São Paulo (Hospital São Paulo) located in São Paulo State, Brazil. Those interested in participation will undergo a detailed screening using the eligibility criteria for enrolment in the study. The sample size was calculated using a statistical software (G^*^Power 3.1.5) on the main outcome measure (i.e., the motor score). This calculation was based on data from five patients (pilot study). The power was 0.80; the α was 0.05, and the effect size was 0.65 (Cohen *d*). The sample estimation indicated that 40 participants would be necessary (i.e., 20 per group), and with an adjustment to allow for a withdrawal rate (20%), we will recruit 50 participants.

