### Randomization

Participants will be randomly allocated to either Group A or Group B with a 1:1 allocation defined by a website (randomization.com). As we will have the participant's characteristics, immediately after the randomization the age and functional capacity (Barthel Index) will be compared between groups. If the groups are not homogeneous, a new randomization will be carried out. This protocol will be repeated until there is no difference between age and Barthel Index among groups (in a maximum of first three attempts at randomization, we always have homogeneous groups). Randomization will be under the control of a blinded investigator who will be the only person allowed to manage the electronic security file of the randomization to locate the individuals. The investigator applying the interventions will then be informed about which group the participant was allocated to so they can conduct the protocol in the correct order of interventions.

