### Assessment Protocol

The assessment protocol will have the following sequence. The functional scale (Barthel Index) will be undertaken first to ensure balance in randomization as this is a key variable. This is followed by group randomization process. After that, assessment scales will be undertaken in a separate room (BRUMS, MRC, and TUG) and one physiological assessment (HRV). The assessment part of the protocol will take around 1 h.

Borg Scale, Spo_2_, RR, and HR will be evaluated before and after each intervention. At the end of each day, ES and VASS questionnaires will be used to determine the individual's final perception of the intervention.

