### Statistical Analysis

Statistical analysis will be performed using IBM-SPSS (version 26.0, IBM Corp., Armonk, NY, USA). As dependent variables, all HRV indices will be considered, as well as test scores of Barthel Index, TUG, MRC, BRUMS, ES, VASS, Borg Scale, Sao_2_, RR, and HR. If the data meet the assumptions of normality, multiple analysis of variance will be used to compare the study groups (virtual group and conventional group) and intragroup comparison (virtual and conventional groups, when comparing the same subject), with least significant difference *post-hoc* test. If the data do not meet the assumptions of normality, the differences between the groups will be analyzed using the Kruskal–Wallis test. Dunn *post-hoc* tests will be performed on each pair of groups, with Dunn–Bonferroni post-test on each pair of groups. The same tests will be applied for *p* < 0.05, which will be considered significant.

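### Both therapies are given on the same day, but the stated analysis leaves out the crossover structure, so unequal carry-over could bias session-level comparisons without being seen

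*Protocol article*

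**What the plan says.** Under Overview of the Study Design, Group A has VR in the morning and then "the conventional intervention in the afternoon (their second rehabilitation session of the day"; Group B has the reverse, "in a crossover design, during the hospitalization period (varying from 2 to 8 days according to individual needs". Table 2 also puts the two therapies on one day, though with a different duration: "Both therapies will be performed on the same day at different times for 10 consecutive days". The article states no interval between sessions and does not argue that residual effects are negligible. Its only reason for two sessions a day is hospital routine.

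What is randomised is the order. Patients are "randomly allocated to either Group A or Group B with a 1:1 allocation" (Randomization).

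Under Statistical Analysis, if the data are normal, "multiple analysis of variance will be used to compare the study groups (virtual group and conventional group", together with an intragroup comparison in the same subject. If they are not, Kruskal–Wallis with Dunn tests is used.

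Borg, SpO2, RR and HR "will be evaluated before and after each intervention" (Assessment Protocol). The Procedure section adds HRV immediately before every therapy, whereas Table 1 marks HRV only on days 1 and 8 and at the two follow-up visits.

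**The concern.** No virtual group or conventional group exists in this trial. There are two sequences, and every patient has both therapies. An afternoon reading may still carry exertion or autonomic change from the morning session. The article itself records HRV around the intervention to study recovery, so it expects some response after a session. The therapies also differ in content: the conventional one includes corridor walking, while VR is played seated or standing at the bedside. Equal residual effects therefore cannot be taken for granted.

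The named analysis separates neither morning from afternoon nor one sequence from the other, and it includes no contrast that would show unequal carry-over. Kruskal–Wallis also treats a patient's two sessions as independent. At stake is the VR-versus-conventional estimate for the session-level measures. These include HRV, the measure behind the autonomic primary outcome in the Primary Outcome section, if it is taken each session.

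**Working it through.** **The plan's own figure.** Recruitment gives these inputs: "The power was 0.80; the α was 0.05, and the effect size was 0.65" (Cohen d), and concludes "40 participants would be necessary (i.e., 20 per group". The figure of 40 is reproduced by a repeated-measures ANOVA with two groups, two measurements, f = 0.65/2 = 0.325 and zero within-patient correlation. Then 40/0.8 = 50. A two-sided two-sample t-test would need 39 per group, and a paired t-test 21 patients. The article names neither the test nor the correlation, so the sample size does not show which contrast was meant. The point below does not depend on it.

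**Bias within one two-session day.** Let τ be the VR-minus-conventional effect and π the afternoon-minus-morning effect. Let λV and λC be the residue of a morning VR or conventional session in the afternoon reading.

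- Group A, mean of VR − conventional: τ − π − λV
- Group B, mean of VR − conventional: τ + π + λC
- Equal-weight average: τ − (λV − λC)/2

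Three things follow.

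1. If λV = λC, the equal-weight average is unbiased.
2. With weight w on Group A, the average is τ + (1 − 2w)π − wλV + (1 − w)λC. With equal carry-over λ this is τ − (2w − 1)(π + λ). Once the groups contribute unequally, even equal carry-over matters, and a morning/afternoon term removes it.
3. Inside one sequence group nothing cancels. With τ = 0.65, π = 0 and λV = λC = 0.325, Group A gives 0.65 − 0.325 = 0.325 and Group B gives 0.65 + 0.325 = 0.975.

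**Size.** The documents give no carry-over figure. Assume that λV − λC is 20% to 50% of the effect. Take τ = 0.65 in units of the SD of the within-patient difference, with 40 patients, a paired t-test and two-sided 0.05.

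| λV − λC | Estimate | Bias | Power (0.98 without bias) | Rejection rate if τ = 0 |
|---|---|---|---|---|
| 0.13 (20%) | 0.65 − 0.065 = 0.585 | 10% | 0.95 | 6.9% |
| 0.325 (50%) | 0.65 − 0.1625 = 0.4875 | 25% | 0.85 | 17% |

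The table understates the effect because VR is assumed to leave the larger residue. If the conventional session does, the sign reverses.

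**Change from the pre-session reading.** Let θV and θC be the carry-over into the afternoon pre-session reading. The change-score bias is −[(λV − λC) − (θV − θC)]/2, which is zero only if the two differences match. If the residue is present before the afternoon session and gone after it, post-session values are unbiased and change scores are not.

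**What a check can do.** The day-1 morning comparison of Group A with Group B precedes any second session. With a two-sided 0.05 t-test it has 80% power for d = 0.81 at 25 per group or 0.91 at 20. At d = 0.65 its power is 0.61 or 0.52. A formal test for carry-over is weaker still. With 20 per sequence and within-patient correlation 0.5 to 0.7 (assumed), its power is 7–9% for a carry-over difference of 0.325 and 13–21% for 0.65.

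**Which outcomes have session-level values.** Borg, SpO2, RR and HR do. HRV does under Procedure but not under Table 1. Barthel, TUG, MRC and BRUMS are taken at the start, on the last day and at follow-up. ES and VASS are asked at the end of the day (Assessment Protocol). All of these later readings follow both therapies.

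**The case against.** A reader might infer that any residue of the morning session must bias the result. The documents do not support that. Equal carry-over cancels in the balanced pooled estimate, the motor part of each session lasts 10 minutes, and nothing shows unequal residues. The 20–50% range is an assumption. The formula also describes one two-session day, while stays run from 2 to 8 days. The order is spelled out only for the first day, and the Introduction speaks of alternating interventions. All of this stands, and it limits the claim to a possible bias of unknown size.

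A second objection is that an article condenses the full plan, so model terms and sensitivity analyses may sit in a document not shown. That is fair as to omitted detail. In particular, silence about the pre-session reading does not prove that it is ignored, and the normal-data option does include a same-subject comparison. The objection does not cover what the section fixes: a comparison of two groups that were never formed, and an independent-samples test on paired readings when the data are not normal.

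A third is that the remedy reaches only some outcomes. That is correct. No carry-over term can recover a therapy effect from a scale taken once after both therapies. Functional capacity, the primary outcome in Table 2, is in that position.

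**Conclusion.** The point holds in limited form. The stated analysis does not reflect the crossover and cannot reveal unequal carry-over in the session-level measures. If the therapies leave unequal residues, the pooled estimate within a two-session day is off by half the difference: 10–25% of the effect for an assumed difference of 20–50%. A comparison made within one sequence group would be biased even by equal carry-over. The documents establish neither that carry-over exists nor that it is unequal. The figures rest on the two-session algebra and on reading 0.65 as a standardised within-patient difference. The change is worth making because it is cheap, not because a bias has been shown.

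**What to change.** Keep the two-session day. For Borg, SpO2, RR and HR, and for HRV if it is measured each session, replace the Statistical Analysis comparison as follows.

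1. Fit a mixed model with therapy, morning/afternoon, sequence and day terms, using the order actually given, and a patient random effect. This restores the pairing and removes time-of-day effects. It does not remove unequal carry-over, which a two-session day cannot separate from sequence, so item 3 is needed.
2. Report results for post-session values and for change from the pre-session reading. State that change scores are unbiased only if the carry-over differences in the two readings match.
3. Add the day-1 morning Group A versus Group B contrast as a sensitivity analysis, free of carry-over from an earlier trial session, and state its low power.
4. Report the day-1 afternoon pre-session readings by group descriptively. Do not use them as a pre-test to choose the main analysis.
5. State that for Barthel, TUG, MRC, BRUMS and end-of-day ES/VASS, Group A versus Group B compares order only and supports no VR-versus-conventional conclusion.
6. Reconcile Procedure with Table 1 on HRV timing. Also reconcile Table 2 with the body text on the number of days, since the day term depends on it.

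The cost is revised wording and a little more analysis. No new data are needed for Borg, SpO2, RR and HR; for HRV that depends on item 6. The drawback is that the sensitivity contrast will be imprecise, so a null result there would not show that carry-over is absent.
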